### Randomization

Based on the sample calculation, we intend to include a total number of 122 patients of which the first 56 patients who agree to participate will be studied using MB-RSA and DXA. The patients are allocated into two groups of equal of size and equally randomized to both arms:
The uncemented Comprehensive Nano stemless shoulder arthroplasty (intervention group)The uncemented Comprehensive stemmed total shoulder arthroplasty (control group)

The randomization is done in the operating theater using the trial laptop just after the perioperative evaluation of the bone-stock and the rotator cuff. Therefore, the patient is anesthetized when the randomization is done. The randomization is done using a computerized irreversible application—the Research Electronic Data Capture (REdCap). The randomization sequence will be computer generated by block randomization stratified for age and gender. The patients are equally randomized to both arms (1:1 allocation). The randomization table has been prepared by an independent statistician.

The patients and the outcome assessor will not be blinded to the randomization allocation. However, the statistician associated with the trial will be blinded.

### Surgical procedure and rehabilitation

All procedures are performed at Copenhagen University Hospital Herlev/Gentofte, which is the largest shoulder arthroplasty unit in Denmark with approximately 250 primary and revision shoulder arthroplasty procedures each year. Based on the number of patients from 2013 to 2016, we expect to operate 50 patients with an anatomical total shoulder arthroplasty for osteoarthritis each year. In order to secure a high surgical standard and to minimize a potential learning curve, the study will be conducted as a single-center study and all patients will be operated on by one of six senior consultant shoulder surgeons with many years of experience and hundreds of shoulder arthroplasties on their resumes. Prior to the initiation of the study, each of the surgeons should have performed at least 3 procedures with the Comprehensive Nano stemless total shoulder arthroplasty. A subgroup analysis, comparing the first half of patients to be included with the second half, is used to discuss the learning curve of the stemless humeral component.

Surgical technique, including exposure instrumentation and soft tissue balancing, is standardized for all patients. The procedure is performed with the patient under general anesthesia in beach chair position. All patients are operated on with the standard deltopectoral approach and subscapularis tenodesis. The patients are treated with either (1) the uncemented Comprehensive Nano humeral component or (2) the uncemented stemmed Comprehensive humeral component according to the guidelines from the manufacturer. The uncemented Comprehensive Nano humeral component is a star-shaped component made of titanium and coated with porous plasma spray. The uncemented stemmed Comprehensive humeral component has a standard stem length of 122 mm and is made of titanium with proximal porous plasma spray coating. A standard Comprehensive Modular Hybrid Glenoid component (Zimmer Biomet, Warsaw, IN, USA) is used in all patients. It is made of polyethylene and consists of three peripheral polyethylene pegs inserted with bone cement and one central titanium peg inserted without bone cement. The humeral bone component is marked with 8–10 RSA markers inserted by the surgeon. Prophylactic cloxacillin 2 g and benzylpenicillin 1.2 g is given preoperative and at 6 and 12 h. If a patient cannot tolerate the standard prophylactic treatment, cefuroxime 1.5 g is given preoperative and at 6 and 12 h. No biological samples will be collected.

All patients have been encouraged to perform non-operative treatment with training, painkillers, possible cortisone injections, and rescheduling of work and leisure activities. If there is no effect of these preoperative treatment attempts, the indication for surgical treatment is given by one of the six senior consultant shoulder surgeons.

Postoperatively, a simple sling will be used for 2 weeks. Before discharge, the patients are instructed to perform edema prophylaxis during the time of immobilization. All patients will follow a standard rehabilitation program supervised by a physiotherapist once a week. Non-weight bearing training is allowed after 2 weeks without any restriction on active external rotation. Weight bearing training is allowed after 6 weeks. There is a minimum of 3 months of training, longer if needed. The patients are allowed to participate in additional rehabilitation if they wish to do so.

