### Trial status

Version 1.4, October 10, 2019.

Start of inclusion: March 1, 2020.

Finnish date of recruitment to the first part of the study (RSA and DXA): February 28, 2021.

Finnish date of recruitment of all 122 patients: March 31, 2022.

Finnish date of follow-up for the first part of the study (RSA and DXA): February 28, 2023.

Finnish date of follow-up for all 122 patients: March 31, 2024.

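### The first-half versus second-half split is a coarse proxy for a surgeon's own stemless experience and, as recruitment is planned, largely coincides with RSA/DXA participation

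*Protocol article*

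**What the plan says.** The learning-curve analysis is set out in one sentence under Surgical procedure and rehabilitation: "A subgroup analysis, comparing the first half of patients to be included with the second half, is used to discuss the learning curve". The sentence goes on to name the stemless humeral component as the target.

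The same section says that "all patients will be operated on by one of six senior consultant shoulder surgeons", and that before the study starts "each of the surgeons should have performed at least 3 procedures with the Comprehensive Nano stemless total shoulder arthroplasty". That is a minimum; no actual counts are given. Under Randomization, allocation is 1:1 and "The randomization sequence will be computer generated by block randomization stratified for age and gender", so surgeon is not a stratification factor. That section also fixes the imaging substudy: "the first 56 patients who agree to participate will be studied using MB-RSA and DXA".

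Trial status gives the planned calendar: "Start of inclusion: March 1, 2020", RSA/DXA recruitment closing on February 28, 2021, and recruitment of all 122 closing on March 31, 2022.

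**The concern.** Learning with a new implant depends on how many of them a given surgeon has already put in. Order of inclusion in the trial is a different quantity. A surgeon with few patients can still be on early stemless cases late in the trial, and a busy one can be well past that stage before the midpoint.

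The midpoint of 122 patients is patient 61, very close to the point at which the RSA/DXA substudy is due to fill. The two halves may therefore differ in substudy participation almost as sharply as in inclusion order.

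The stake is interpretive. A difference between halves could be put down to learning when it reflects time or substudy membership, and a real learning effect could be diluted. Migration matters most here: it is a primary outcome measured only in the substudy, so the split may leave nothing to compare.

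**Working it through.** **Size of the halves.** The WOOS calculation (SD 15, difference 10, 5% two-sided assumed, power 0.90) reproduces at 48 per group. 48/0.80 = 60 per group, or 120, against the stated 122. The RSA calculation (SD 0.4, difference 0.4) reproduces at 22 per group; 22/0.80 = 27.5, rounded up to 28, gives 56. The halves are 122/2 = 61 each.

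**Own experience against trial half.** With 1:1 allocation there are about 61 stemless operations, or 61/6 = 10.2 per surgeon and about 5 per half. The protocol article gives no caseload shares, so these are assumed. I simulated 122 patients in blocks of four, assigned surgeons at random by share, and counted each surgeon's stemless cases. Adding the same 3 prior cases to every surgeon does not change R².

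| Assumed shares (%) | R² of half with own case number | Chance that a second-half stemless case has no more own experience than a first-half one |
|---|---|---|
| equal | 0.53 | 0.09 |
| 35/25/15/10/10/5 | 0.38–0.39 | 0.16 |
| 40/25/15/10/6/4 | 0.37 | 0.17 |
| 50/20/10/10/5/5 | 0.32 | 0.20 |

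For scale, a perfect median split of a uniformly distributed count has R² = (1/16)/(1/12) = 0.75, so the ceiling for any two-group split is about 0.75 rather than 1.

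**Overlap with RSA/DXA.** From March 1, 2020, RSA recruitment closes on day 364 and all recruitment on day 760. At an even rate, 122 × 364/760 = 58.4 patients would be in by day 364. Filling 56 RSA places by then needs 56/58.4 = 96% acceptance. Patient 61 would then arrive at about day 364 + (5/66) × 396 = 394, or month 13.

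| | RSA/DXA | not RSA/DXA |
|---|---|---|
| First 61 | 56 | 5 |
| Last 61 | 0 | 61 |

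Participation is 56/61 = 92% against 0%. Agreement is (56 + 61)/122 = 95.9%. Phi = (56 × 61 − 5 × 0)/√(61 × 61 × 56 × 66) = 3416/3708.5 = 0.92.

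This depends on acceptance, which the protocol article does not state:

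| Assumed acceptance | RSA in first half | RSA in second half | phi |
|---|---|---|---|
| 92% or more | 56 | 0 | 0.92 |
| 90% | 54.9 | 1.1 | 0.89 |
| 80% | 48.8 | 7.2 | 0.68 |
| 70% | 42.7 | 13.3 | 0.48 |
| 50% | 30.5 | 25.5 | 0.08 |

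**Precision.** If the halves were compared through an arm-by-half interaction in WOOS, with SD 15 and 24 completers in each of four cells, SE = 15 × √(4/24) = 6.12 and the 95% half-width is 1.96 × 6.12 = 12.0 points. Without drop-out (30.5 per cell) it is 10.6. The plan does not specify this interaction. The figure shows only what 122 patients can support, and it limits any replacement analysis in a similar way.

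**The case against.** The strongest reply is that little rests on this analysis. It serves discussion only; it is not a hypothesis, a listed outcome or part of either primary test. Learning is also limited by design, through a single centre, senior surgeons and a minimum number of prior cases. All of that stands and sets the severity.

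Several stronger readings are tempting, and the protocol article does not support them:

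- A reader might infer that the split says nothing about experience. It does carry information: an R² of 0.37 to 0.53 is a correlation of about 0.6 to 0.7, against a ceiling of 0.75 in R² for a perfect two-group split.
- A reader might infer that the overlap with RSA/DXA is certain. It follows from the planned dates, but the substudy takes those who agree, and the RSA sample size section names unwillingness to participate as a risk. At an assumed 70–80% acceptance phi is about 0.5 to 0.7.
- A reader might infer that RSA patients attend extra visits that could alter WOOS. Follow-up gives everyone the same evaluation times, and the two schedule figures are not shown.
- A reader might infer that the arms are bound to be pooled. The sentence does not say how they are handled, and an article may leave that to the full protocol.
- A reader might infer that treatment is confounded with RSA status. RSA patients are in both arms, so any overlap in an arm-by-half contrast is with arm-by-RSA status.

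**Conclusion.** The point holds as a low-severity improvement. The stated split is a coarse stand-in for a surgeon's own stemless case number: about half of the variance with equal caseloads, and about 37% under the assumed 40/25/15/10/6/4% shares (32–39% over the uneven patterns tried).

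If recruitment follows the stated sequence and dates, the split also nearly coincides with RSA/DXA participation (56 of 61 against about 0 of 61). A 61/61 split then has no second-half migration data, and that conclusion needs no caseload assumption. Halving the 56 RSA patients separately would allow a migration comparison, but the text does not say this. The overlap result rests on high RSA acceptance and weakens as more patients decline.

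Neither primary comparison is affected.

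**What to change.** Keep the analysis exploratory, and replace the split, or report alongside it, as follows.

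- Define experience as the operating surgeon's cumulative number of stemless procedures at the date of surgery, pre-trial cases included. Record each surgeon's pre-trial count, because the protocol article requires only a minimum of three and not a recorded number.
- Enter it as a continuous term, with its interaction with arm, in the mixed model already planned. The interaction is the learning effect; the stemmed arm absorbs general drift over time.
- Adjust for surgeon. With only six, a fixed effect is acceptable and a random intercept would be weakly estimated.
- Adjust for RSA participation as a sensitivity analysis only. If recruitment runs as planned, it is so close to inclusion order that routine adjustment could remove much of the experience contrast.
- For MTPM, examine case number within the 56 RSA patients.
- State that precision is limited and that a null result does not show absence of learning.

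The cost is analysis wording, a slightly more complex exploratory model and writing down the pre-trial counts. Surgeon and operation date should be available from the surgical record. Sample size, visits and both primary analyses are unchanged.

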### Outcome measures

#### Primary radiological outcome

##### Magnitude of migration of the humeral component assessed by MB-RSA

The MB-RSA will be performed according to the guidelines by Valstar and Colleagues [15]. RSA is used to measure humeral component migration. Fifty-six patients will be included in this part of the study. Maximum total point motion (MTPM) after 2 years compared to the baseline value will be used as the primary RSA effect parameter. The precision of RSA will be evaluated by at least 12 double examinations. RSA is performed using a uniplanar RSA arrangement (UmRSA®-Calibration Cage No 43 (hip, spine, and shoulder)). The analysis of x-rays will be performed using the MB-RSA commercial software (RSAcore, Department of Orthopedics, Leiden University Medical Center, Leiden, The Netherlands), available at Skaane University Hospital, Lund Sweden, where analyses of RSA-x-rays will be performed using a well-established research cooperation with consultant orthopedic surgeon, PhD, [name]. The precise set-up for the RSA arrangement (e.g., various distances and the degree between the 2 x-ray tubes) will be determined from a small phantom study and measurements of the 6 pilot patients (3 with each of the 2 types of implants). In addition, the pattern of migration of the humeral component assessed by MB-RSA will be presented using descriptive statistics, but without the performance of statistical tests.

#### Primary functional outcome

##### Western Ontario Osteoarthritis of the Shoulder index (WOOS)

The WOOS is a disease-specific patient-reported outcome [37]. There are 19 questions divided into four domains: physical symptoms, sports and work, lifestyle, and emotions. Each question is answered on a visual analogue scale ranging from 0 to 100. The overall score ranges from 0 to 1900, with 1900 being the worst. For ease of interpretation, the scores are converted to a percentage of the maximum score. The primary value of interest is the difference in mean score between the preoperative score and 2-year follow-up. We use a Danish version of WOOS which was translated according to the guidelines of Guillemin, Bombardier, and Beaton [38]. It was validated with classical test theory in a cohort of patients treated with shoulder arthroplasty for osteoarthritis [39]. No minimal clinically important difference for WOOS has been reported yet.

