### Statistics

The nature of data is evaluated before the analysis. The between-group differences are expected to be analyzed with independent *t* test (Student *t* test). If the assumption of normal distribution is violated, then data will be analyzed with non-parametric tests. We do not expect the RSA data to be normal distributed. These data will be analyzed with non-parametric analysis using the Friedmann test for migration over time and the Mann-Whitney *U* test for between-group differences. We expect the DXA data to be normally distributed and changes over time will be evaluated by a parametric analysis using a paired *t* test. Potential between-group differences in BMD changes will be analyzed with independent *t* test (Student *t* test). In addition, due to the nature of repeated measures in this study, we intend to analyze the overall results according to a mixed effects model [45]. The difference between pre- and postoperative scores is expected to be analyzed as a secondary endpoint with parametric analysis using a paired *t* test. Since the two primary endpoints are distinct, multiple testing adjustments will not be performed.

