#### Sample size calculation WOOS

With a standard deviation of WOOS of 15 (15% of a maximum score), a difference of 10 (10% of a maximum score), a significance level of 5%, and a power of 0.90, 48 patients are needed in each group resulting in a study population with 122 participants [46] (allowing for 20% drop-out). No minimally clinically important difference of the WOOS score has ever been reported. Therefore, it is important to mention that the use of 10 points in this study is an arbitrary value.

Data on RSA and DXA will be analyzed at the end of follow-up for 56 patients. We have chosen not to perform a 1-year formalized interim analysis, but an external independent assessor from another hospital will once a year get an update on the study and review the results in a confidential manner. In this way, the scientific validity of the study will be improved.

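### The primary WOOS change is tested without baseline or strata adjustment, and the SD of 15 behind the 90% power is not identified as that of the score or of the change

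*Protocol article*

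**What the plan says.** - **Endpoint.** The WOOS section under primary functional outcome states: "The primary value of interest is the difference in mean score between the preoperative score and 2-year follow-up". Read plainly, this is a change score.
- **Test.** The Statistics section says "The between-group differences are expected to be analyzed with independent" t test, with a non-parametric fallback. No covariate is named. The same section adds that "we intend to analyze the overall results according to a mixed effects model", introduced as an addition to the t test.
- **Status of the pre/post difference.** The Statistics section also says: "The difference between pre- and postoperative scores is expected to be analyzed as a secondary endpoint with parametric analysis using a paired" t test.
- **Sample size.** The WOOS sample size section begins: "With a standard deviation of WOOS of 15 (15% of a maximum score), a difference of 10 (10% of a maximum score". It adds a 5% significance level and power of 0.90, arriving at 48 per group and 122 in total with 20% drop-out. It does not say whether 15 refers to the score or to its change, and gives no correlation between visits.
- **Randomisation.** The Randomization section says: "The randomization sequence will be computer generated by block randomization stratified for age and gender". Neither factor appears in a stated test.

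**The concern.** The SD in a sample size calculation has to be the SD of the quantity tested. A change score carries the variability of two measurements. Unless the visits are correlated strongly enough, its SD exceeds that of a single score. The wording of the calculation can be read as the SD of the score, while the endpoint section describes a change. On that reading, the stated 90% power depends on a correlation the protocol never gives. The WOOS calculation also sets the total of 122.

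The second issue is efficiency. Preoperative WOOS is collected before surgery but is used only by subtraction, which fixes its coefficient at 1 instead of estimating it. With equal SDs and a correlation below 1, that over-corrects a chance baseline difference. Ignoring the strata leaves the standard error larger than necessary if age or gender predicts outcome.

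The third issue is that the sentence calling the pre/post difference secondary sits awkwardly beside the endpoint section. It leaves open which WOOS quantity is primary.

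**Working it through.** **Inputs.** From the WOOS sample size section: SD 15, difference 10, 5% level, power 0.90, 48 per group, 20% drop-out. From the Randomization section: 1:1 allocation. Assumptions: two-sided testing (sidedness is not stated), and the correlation r between preoperative and 2-year WOOS, shown over a range because the protocol does not give it.

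**Reproducing the plan's figure.** n per arm = 2 × (1.960 + 1.282)² × 15² / 10² = 47.3, rounded up to 48. The t-based solution is 48.3. Power at 48 per arm is 0.904 (normal) or 0.898 (t). For the total, 96 / 0.8 = 120, within 2 of the stated 122. So 48 holds with 15 as the SD of the analysed variable.

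**If 15 is the SD of the score at both visits.**
- SD of change = 15 × √(2(1 − r))
- Residual SD for ANCOVA on the 2-year score = 15 × √(1 − r²)
- Variance ratio, change to ANCOVA = 2(1 − r) / (1 − r²) = 2 / (1 + r)

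Two-sample power at 48 per arm, difference 10:

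| r | SD of change | Power, change | ANCOVA SD | Power, ANCOVA | Variance ratio |
|---|---|---|---|---|---|
| 0 | 21.21 | 63% | 15.00 | 90% | 2.00 |
| 0.2 | 18.97 | 72% | 14.70 | 91% | 1.67 |
| 0.3 | 17.75 | 78% | 14.31 | 92% | 1.54 |
| 0.4 | 16.43 | 84% | 13.75 | 94% | 1.43 |
| 0.5 | 15.00 | 90% | 12.99 | 96% | 1.33 |
| 0.6 | 13.42 | 95% | 12.00 | 98% | 1.25 |
| 0.7 | 11.62 | 99% | 10.71 | over 99% | 1.18 |

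The break-even correlation for 90% power is 0.49 (normal) or 0.50 (t). Below it, the change score would need 58 per arm at r = 0.4, 68 at 0.3 and 77 at 0.2.

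**If the SDs differ between visits.** Write s₀ for the preoperative SD and s₁ for the 2-year SD. The variance of change is s₀² + s₁² − 2r·s₀·s₁, which equals s₁² when r = s₀ / (2s₁). With s₁ = 15, the break-even is 10/30 = 0.33 for s₀ = 10 and 20/30 = 0.67 for s₀ = 20.

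**If 15 is the SD of the change, or the 2-year score is compared.** The analysed variable has SD 15, and 48 per arm gives the stated 90% whatever r is.

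**Precision of adjustment under any reading.** The variance of change can be rewritten as (s₀ − r·s₁)² + s₁²(1 − r²). The second term is the ANCOVA variance, so ANCOVA is never the less precise of the two, apart from the small cost of estimating the slope. With equal SDs it is strictly better than the change score for any r below 1, and better than the 2-year score alone for any non-zero r.

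**The case against.** The strongest reply is that the protocol shows an unlabelled SD, not a wrong one. Since the endpoint section defines a pre-to-2-year difference, 15 may have been meant for that difference, and then nothing is amiss with the 48. If instead the secondary-endpoint sentence means the 2-year score is primary, 15 also fits. Lost power needs two readings together: change is primary, and 15 is the SD of the score. This stands. A reader might infer that the trial was sized with the wrong SD or is underpowered. The document supports neither, because it gives no correlation and does not identify the SD.

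Further points also hold:
- The 0.5 threshold depends on equal SDs at the two visits.
- The table assumes the full drop-out allowance is used up. With all 61 per arm retained, change-score power is 87.5% at r = 0.3 and 92% at r = 0.4 (normal approximation).
- Under randomisation the unadjusted change-score comparison is unbiased, and omitting the strata makes it conservative if anything. No figure in the protocol shows how much age or gender matters.
- The 10-point difference is declared arbitrary, so nominal power is soft in any case.
- The secondary-endpoint sentence names a paired test and most naturally covers within-group improvement.

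The planned mixed model could recover the precision, and the section on protocol violations and drop-out says drop-outs enter it. Its covariates may properly sit in an analysis plan that is not shown. But the Statistics section presents it as additional to the t test, and the sample size formula is that of a simple two-group comparison. It does not settle which result is primary.

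**Conclusion.** The point holds as a matter of clarity and efficiency. It should be fixed, but it does not invalidate the analysis. The stated 90% power for WOOS is conditional on something the protocol leaves unsaid. It stands if 15 is the SD of the change or if the 2-year score is compared. If 15 is the score SD at both visits and change is tested, it stands only for a correlation of about 0.5 or more. That threshold moves between about 0.33 and 0.67 for a preoperative SD of 10 to 20 with a 2-year SD of 15. A shortfall is possible, not demonstrated.

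The case for adjustment does not rest on resolving that question. With equal SDs, the change score has 1.67 to 1.33 times the ANCOVA variance at correlations of 0.2 to 0.5, and ANCOVA is at least as precise at every correlation.

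**What to change.** 1. Make the primary WOOS estimate the between-arm difference at 2 years, adjusted for preoperative WOOS, age and gender. Obtain it either from ANCOVA or from the 24-month contrast of the mixed model already planned, and name one of them as primary. If change is the preferred way to report, ANCOVA on the change with preoperative WOOS as a covariate gives the same between-arm estimate.
2. In the WOOS sample size section, state whether 15 is the SD of the score or of the change. Only the sponsor can say which was meant. If it is the score SD, tie the power statement to the baseline-adjusted analysis or give the assumed correlation.
3. Reconcile the WOOS endpoint section with the secondary-endpoint sentence in Statistics, for example by saying that the paired test describes within-group improvement only, if that is the intention.
4. The same baseline adjustment can be used for the other scores measured before surgery (OSS, Constant-Murley, VAS pain). BMD can keep its planned adjustment through bilateral measurements.

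The cost is a few sentences. Preoperative WOOS, age and gender are already collected at enrolment, so no patients, visits or data are added. The wording should be settled before outcome data are examined.
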